**Central Sensitisation Inventory**

**Please circle/tick the best response to the right of each statement**

| 1. I feel tired and unrefreshed when I wake from sleeping. | Never | Rarely | Sometimes | Often | Always |
| --- | --- | --- | --- | --- | --- |
| 2. My muscles feel stiff and achy. | Never | Rarely | Sometimes | Often | Always |
| 3. I feel pain all over my body. | Never | Rarely | Sometimes | Often | Always |
| 4. I have headaches. | Never | Rarely | Sometimes | Often | Always |
| 5. I do not sleep well. | Never | Rarely | Sometimes | Often | Always |
| 6. I have difficulty concentrating. | Never | Rarely | Sometimes | Often | Always |
| 7. Stress makes my physical symptoms get worse. | Never | Rarely | Sometimes | Often | Always |
| 8. I have muscle tension in my neck and shoulders. | Never | Rarely | Sometimes | Often | Always |
| 9. I have difficulty remembering things. | Never | Rarely | Sometimes | Often | Always |

| **CLINICAL INFLAMMATION SCORE** | |
| --- | --- |
| 1. **Constant Symptoms**   Are your symptoms constantly with you 24 hours a day even when you rest or gently walk?   yes   no   1. **Morning pain/stiffness**   In the past 3 days have you had a painful or stiff back in the morning?   yes   no  If so, how long does it take for the pain/stiffness to ease if you don't take medication?   Less than 30 minutes   30-60 minutes   greater than 1 hour   constant pain/stiffness all day   I always take medication   1. **Easing factors**   Is your pain EASED by walking short distances (eg. one block)?   yes   no | 1. **Night symptoms**   **4a) Waking**  In the past 3 days how often have the symptoms woken you while sleeping?   not at all   some nights   most nights   every night  **4b) Reason for waking**  In the past 3 days if the symptoms have woken you, what has been the reason?   not applicable   rolling over   wake due to pain without moving   Other  **4c) Return to sleep**  In the past 3 days if the symptoms have woken you, what have you done so you can go back to sleep?  Please tick one box only (the thing you usually do to get back to sleep)   not applicable   nothing helps, can't fall back to sleep   change positions in bed   sit up   get out of bed   take medication   Other |

**Treatment Credibility Questionnaire**

We would like you to indicate below how much you believe, *right now*, that the treatment you are about to receive / are receiving will help you with your back problem.

**1) At this point, how logical does the treatment offered to you seem?**

0 1 2 3 4 5 6 7 8 9 10

*Not at all logical Somewhat logical Very logical*

**2) At this point, how successful do you think this treatment will be in helping you with your back problem?**

0 1 2 3 4 5 6 7 8 9 10

*Not all successful Somewhat successful Very successful*

**3) How confident would you be in recommending this treatment to a friend who experiences similar problems?**

0 1 2 3 4 5 6 7 8 9 10

*Not at all confidence Somewhat confident Very confident*

**4) By the end of your treatment, how much improvement in your back condition do you think will occur?**

0% 10% 20% 30% 40% 50% 60% 70% 80% 90% 100%

*No improvement Moderate improvement Complete improvement*

## APPENDIX 2: CLASSIFICATION INTO SUBGROUPS AND TREATMENT

| **Classification into subgroups ^[1-10]^** |
| --- |
| 1. **Disc herniation with associated radiculopathy** |
| To be classified in this subgroup, participants will have at least 2 of the following 3 diagnostic criteria:   1. referred leg symptoms (below the knee for L4/5 or L5/S1 herniations, or into the anterior thigh for L1/2, L2/3 or L3/4 herniations), 2. reproduction of usual leg symptoms on straight leg raise (SLR) or reproduction of usual anterior thigh symptoms on prone-knee-flexion testing in combination with the Hancock rule [1] comprising at least 3 positives out of 4 clinical examination signs suggestive of radiculopathy: 3. pain location in concordance with a nerve root, 4. corresponding sensory deficit (reduced dermatomal sensation, 5. corresponding reflex deficit (reduced reflex), 6. motor weakness (reduced myotomal strength) [2] and, 7. a Computerised Tomography (CT) or Magnetic Resonance Imaging (MRI) scan demonstrating a lumbar disc herniation consistent with #i or #ii above [3]. |
| 1. **Reducible discogenic pain** |
| To be classified in this subgroup, participants will present with at least 4 out of 9 features indicative of discogenic low back pain. The features have been identified through literature searching, consideration of causal mechanisms and the results of a Delphi study of experts in the field [4]. The features are:  1) Presence of low back pain with or without leg pain  2) Sitting limited to less than 60 minutes  3) Symptoms worse the next morning or next day following the initial injury  4) History of working in a job involving manual handling  5) A mechanism of injury associated with flexion/rotation and/or compression loading  6) At least some difficulty with forward bending  7) At least some difficulty with lifting  8) At least some difficulty with sit-to-stand  9) At least some difficulty with coughing/sneezing.  Participants will also demonstrate a directional preference in response to mechanical loading strategies on physical examination. The presence of a directional preference has been proposed as identifying people likely to have discogenic pain where a posterior or posterolaterally migrated nucleus pulposus can be “reduced” into a more central and non-pain provoking position [5-7]. |
| 1. **Non-reducible discogenic pain** |
| To be classified in this subgroup, participants will have at least 4 out of 9 signs of discogenic pain as outlined above for the reducible discogenic pain subgroup. However, participants who do not demonstrate a directional preference in response to mechanical loading strategies will be classified in the non-reducible (rather than reducible) discogenic pain subgroup provided they do not satisfy the selection criteria for the zygapophyseal joint dysfunction group [8]. |
| 1. **Zygapophyseal joint dysfunction** |
| This group will comprise participants believed to have zygapophyseal joint dysfunction as the primary source of their back symptoms. To be classified in this subgroup, participants will have at least 3 of the following 4 features of zygapophyseal dysfunction:   1. presence of unilateral low back pain, 2. a regular compression pattern (pain reproduced with lumbar extension and ipsilateral lateral-flexion movements), 3. localized pain on ipsilateral passive postero-anterior accessory movement applied through the transverse process or the zygapophyseal joint at one or two segments and, 4. improvement in pain or range-of-movement following a “mini-treatment” of manual therapy directed at the zygapophyseal joint [9]. |
| 1. **No identifiable pathoanatomical** |
| Participants without a clear pathoanatomical classification (ie. They do not fit one of the other four pathoanatomical subgroups), who also have an Orebro Musculoskeletal Pain Questionnaire score greater than 105, will be classified as belonging to this subgroup. In these participants it is hypothesized that psychosocial and/or neurophysiological factors may be negatively impacting their recovery [10]. |
| 1. **Others:**   Participants other pathoanatomical disorder (ie. They do not fit one of the other four pathoanatomical subgroups) |

Additionally, patients in all STOPS subgroups will be further evaluated according to

1. To their dominant pain type (nociplastic, neuropathic or nociceptive) using validated assessment criteria ^[11-16]^.
2. Psychosocial barriers to recovery, evaluated via the Orebro Musculoskeletal Pain Questionnaire^[17]^, Depression, Anxiety and Stress Scale^[18]^, Pain Self-Efficacy Questionnaire^[19]^ and Pain Catastrophising Scale ^[20]^.
3. Suspected presence of inflammation based on a validated symptom screening tool ^[21]^

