## 2.6 Participants

The initial selection criteria outlined in Table 1. Eligible patients will be informed about the study and will be invited to participate by signing a written informed consent before being enrolled.

| **Inclusion criteria** |
| --- |
| 1. A primary complaint of either:   1. low back pain, defined as pain between the inferior costal margin and the inferior gluteal fold with or without referral into the leg(s),   or   1. referred leg pain, defined as predominately unilateral posterior leg pain extending below the knee, or anterior thigh pain, with or without back pain (disc herniation with associated radiculopathy subgroup only)   2. Duration of the current episode of primary complaint lasting for greater than 3 months (chronic stage of the injury)  3. Aged between 18 and 65 (inclusive)  4. Fluency in English sufficient to complete questionnaires and to enable understanding of the intervention  5. Agreeing to refrain from other interventions wherever possible for the 10-week treatment period of the trial, aside from consultations with medical practitioners, medication, and any exercises already being undertaken. |
| **Exclusion criteria** |

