## 2.8 Baseline evaluation

In addition to demographic and general health information of the participant, all the outcome measures (Table 2) provided below will be evaluated at baseline for both STOPS group as well as standard physiotherapy group. All the baseline assessment will be performed by a Physiotherapist who has a minimum of bachelor level degree and blinded allocation of the groups.

| **Patients’ outcome measures** | |
| --- | --- |
| **Outcome measures** | **Measurement points (**weeks) |
| **Primary outcome measures** | |
| 1. Oswestry Disability Index V2.1 with “sex life” question replaced by a “work/housework” question | 0, 5, 10, 26 and 52 |
| 2.Back pain and leg pain intensity :NPRS | 0, 5, 10, 26 and 52 |
|  |  |
| 3. Resting state functional MRI | 0,26 |
| **Secondary outcome measures** | |
| 1. Brief Pain Inventory | 0, 5, 10, 26 |
| 1. Global rating of change scale (7-point Likert scale) | 5, 10, 26 |
| 1. Satisfaction with treatment (5-point Likert scale) | 5, 10, 26 |
| 1. Interference with work or housework in the past week (5-point Likert scale) and number of hours missed at work in past week. | 0, 5, 10, 26 |
| 1. Örebro Musculoskeletal Pain Screening Questionnaire (ÖMPSQ-SF) | 0, 5, 10, 26 |
| 1. Quality of life (EuroQol-5D-5L) | 0, 5, 10, 26 |
| 1. Depression Anxiety and Stress Scale (DASS-21) | 0, 5, 10, 26 |
| 1. Pain Self-Efficacy questionnaire (PSEQ) | 0, 5, 10, 26 |
| 1. Pain Catastrophizing Scale (PCS) | 0, 5, 10, 26 |
| 1. Insomnia Severity Index (ISI) | 0, 5, 10, 26 |
| 1. Central Sensitisation Inventory (CSI) | 0, 5, 10, 26 |
| 1. Clinical inflammation score | 0, 5, 10, 26 |
| 1. Treatment Credibility Questionnaire | 5, 10, 26 |
| 1. Healthcare utilisation | 5, 10, 26 |
| 1. Compliance with treatment | 5, 10, 26, 52 |
| 1. Resting state functional MRI | 0, 26 |
| 1. Qualitative interviews | At the end of treatment trial 10 |
| 1. Adverse event | 5, 10, 26 |

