## 2.10 Interventions

### 2.10.1 STOPS group

***Classification of patients into subgroups***

Those found to be eligible will be invited to attend individualized assessment with trained physiotherapists. Information from the initial eligibility criteria and physical examination (Appendix 1) will be used to confirm eligibility, determine which subgroup (if any) the patient fits and provide descriptive information on the baseline characteristics of the patients. The patients will be classified into one of the five pre-defined subgroups; i) disc herniation with associated radiculopathy, ii) reducible discogenic pain, iii) non-reducible discogenic pain, iv) zygapophyseal joint dysfunction, v) Sacroiliac dysfunction vi) Non identifiable pathoanatomical disorder, or vii) others subgroup based on information from the eligibility criteria and physical examination. Additionally, patients in all STOPS subgroups will also be further evaluated according to their dominant pain type (nociplastic, neuropathic or nociceptive) using validated assessment. The detailed justification for each of the subgroups has been reported in the previous STOPS classification and treatment protocols.^[14,56-63]^ Additionally, an overview and description of the subgroups is reported in Appendix 2.

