**Pathoanatomical diagnosis (if any)**

**Deconditioning**

**Stage 3:**

**Potential barriers to recovery**

**Figure 2: STOPS decision rule algorithm for classifying participants into subgroups**

**STOPS treatment**

Patients will receive individualized physiotherapy sessions, specific to each subgroup, over 10 weeks. The protocols for each subgroup will be outlined in a detailed treatment manual, supplemented by clinical notes which will contain an outline of the treatment protocol including a series of decision-making algorithms on a session-by-session basis. The algorithms (Figure 2) and clinical notes will ensure that essential elements of the treatment program are consistently applied by all physiotherapists across all patients, while still allowing some opportunity for the treatment to be tailored to individual patients. The clinical notes will also require the physiotherapists to document assessment or reassessment findings, clinical reasoning or decision-making rationale, treatment provided and response to treatment during each session. A detailed description (Appendix 2) of the treatment methods, clinical notes and decision-making algorithms for each subgroup will be based broadly on the principles outlined in the Specific Treatment of Problems of the Spine (STOPS) trial treatment protocols. ^[14,56-63]^ A summary of the treatment components is outlined in Table 3.

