6. *Psychosocial risk factors:* The Short-Form Örebro Musculoskeletal Pain Screening Questionnaire (ÖMPSQ-SF) will be used as a measure of psychosocial risk factors for chronic musculoskeletal pain ^[83,84]^. Although it is more commonly used as a prognostic screening tool at one point in time ^[85]^, in our trial the Orebro will also be administered at each follow-up point to detect changes in psychosocial risk factors over time. This appears justified given that Orebro has good test-retest reliability and internal consistency ^[83,86]^.
7. *Health-related quality of life:* Health-related quality of life will be measured with the EuoQol-5D-5L ^[87]^. Utilities will be calculated according to the validated algorithms of Dolan ^[88]^. The EuroQol-5D-5L has good reliability, validity, and ^responsiveness [89-91]^, and has been used in other low back pain trials ^[64,92]^.
8. *Mental health symptoms:* Mental health symptoms will be assessed using the 21-item Depression Anxiety and Stress Scale (DASS-21). The questionnaire measures the severity of depression, anxiety, and stress from normal to extremely severe ^[93]^. DASS-21 normal score cut-offs are 9 for depression, 7 for anxiety, and 14 for stress and higher scores suggest mild to extremely severe mental health symptoms ^[93]^. DASS-21 shows strong validity, test-retest reliability, internal consistency, and responsiveness ^[93,94]^.
9. *Confidence with activities:* Confidence with activities of daily living despite having pain will be assessed using the Pain Self-Efficacy Questionnaire (PSEQ). The PSEQ is a 10-item scale with a score ranging from 0 to 60, where high scores indicate greater levels of confidence in dealing with pain ^[95]^. The PSEQ has excellent validity, reliability, and responsiveness ^[96]^.
10. *Pain catastrophising:* The 13-item Pain Catastrophizing Scale (PCS) will be used to assess inappropriate coping strategies and catastrophic thinking about LBP. The scale is rated on a 5-point Likert scale ranging from 0 (not at all) to 4 (all the time) ^[97]^. Total scores range from 0 to 52, with higher scores indicating worse catastrophic thinking about LBP ^[97]^. The PCS has been shown to have adequate validity, reliability and responsiveness ^[97,98]^.

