# Orebro Musculoskeletal Pain Screening Questionnaire

1. **How long have you had your current pain problem? Tick one**

0-1weeks [1] 1-2 weeks [2] 3-4 weeks [3] 4-5 weeks [4] 6-8 weeks [5]

9-11 weeks [6] 3-6 months [7] 6-9 months [8] 9-12 months [9] over 1 year [10]

1. **How would you rate the pain that you have had during the past week? Circle one.**

0 1 2 3 4 5 6 7 8 9 10

*No pain* *Pain as bad as it could be*

1. **How tense or anxious have you felt in the past week? Circle one. How much have you been bothered by feeling depressed in the past week? Circle one.**

0 1 2 3 4 5 6 7 8 9 10

*Absolutely calm and relaxed* *As tense and anxious as I’ve ever felt*

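### The Örebro cut-off of more than 105 for the 'No identifiable pathoanatomical' subgroup cannot be reached on the ten-item form that the protocol prints, which has a maximum of 100

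*Protocol*

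**What the plan says.** Appendix 2 of the protocol defines the *No identifiable pathoanatomical* subgroup by two conditions. The patient fits none of the pathoanatomical subgroups, and the patient must be among those "who also have an Orebro Musculoskeletal Pain Questionnaire score greater than 105, will be classified as belonging to this subgroup". The appendix adds the hypothesis that psychosocial or neurophysiological factors are holding back recovery in these patients. The next entry, *Others*, reads "Participants other pathoanatomical disorder (ie. They do not fit one of the other four pathoanatomical subgroups".

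The questionnaire is named with its version in two places. Table 2 (section 2.8) schedules the "Örebro Musculoskeletal Pain Screening Questionnaire (ÖMPSQ-SF" at weeks 0, 5, 10 and 26. Section 2.12, Secondary outcomes, item 6 says: "The Short-Form Örebro Musculoskeletal Pain Screening Questionnaire (ÖMPSQ-SF) will be used as a measure of psychosocial risk factors". No other Örebro version is scheduled or printed.

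Section 2.10.1 lists the subgroups by name, ending with "vi) Non identifiable pathoanatomical disorder, or vii) others subgroup based on information from the eligibility criteria and physical examination", and sends the reader to Appendix 2 for their description. Under STOPS treatment, patients are to receive "individualized physiotherapy sessions, specific to each subgroup, over 10 weeks".

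**The concern.** A cut-off has to lie within the range of the score it is applied to. Here the cut-off is given without a version, while the version scheduled is a short form whose printed items appear to sum to less than 105. If so, one defined branch of the STOPS classification can never be used.

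Classification is the first step of the experimental treatment. Sessions are described as subgroup-specific, and Table 3 has the researchers check video recordings and patient notes against the treatment protocols. A therapist and a fidelity assessor faced with a patient who fits no pathoanatomical class both need a rule that can be met. With the present rule, a patient whose difficulties are mainly psychosocial cannot receive the label written for that patient. The nearest alternative is a label for some other pathoanatomical disorder.

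**Working it through.** **Inputs**

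- Cut-off: above 105 (Appendix 2).
- Version: short form only (Table 2; section 2.12, Secondary outcomes, item 6).
- Item 1, pain duration: coded 1 to 10. The upper codes are "3-6 months [7] 6-9 months [8] 9-12 months [9] over 1 year [10".
- Items 2 to 10: one 0-to-10 scale each, for pain, tension, depression, risk of persistence, chance of working, two belief statements, light work and sleep. That makes nine scales.
- Eligibility (Table 1): "Duration of the current episode of primary complaint lasting for greater than 3 months".

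**Range of the printed form, taking the total as the sum of the ten items**

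1. Maximum = 10 + 9 × 10 = 100. Items marked for reverse scoring become 10 minus the circled number, which still runs from 0 to 10, so the maximum does not move.
2. Minimum for an eligible patient: symptoms beyond 3 months give at least 7 on item 1, so 7 + 9 × 0 = 7.
3. Attainable range for an eligible patient: 7 to 100.
4. Lowest whole score above 105 is 106. Shortfall = 106 − 100 = 6 points.

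On this form the share of patients who can qualify is therefore zero.

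**How far the result depends on reading the form as printed**

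| Reading | Maximum | Can 105 be exceeded? |
|---|---|---|
| Ten items as printed | 10 + 90 = 100 | No |
| Duration item not scored | 9 × 10 = 90 | No |
| Doubled stem of item 3 counted as two answers | 100 + 10 = 110 | Yes |
| Three further activity items assumed, 0 to 10 each | 100 + 3 × 10 = 130 | Yes |

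The third reading fails on the page: item 3 has a single response scale, and depression is asked separately as item 4. The fourth reading arises because the activities stem announces five activities and two are printed. The documents show no further items and name only a short form, but the mismatch is visible and has to be settled against the instrument itself.

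**What follows from an unattainable cut-off**

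- *No identifiable pathoanatomical* and *Others* both start from not fitting the other classes. The Örebro score is the only measured criterion that separates them.
- With that criterion out of reach, a patient who fits no class is either labelled *Others* or left without a label. Section 2.10.1 allows for a patient who fits no subgroup.
- In Appendix 2, STOPS Physiotherapy, the treatment components are chosen from assessment findings, and none is tied to either residual label. Pain type and psychosocial barriers are assessed in every STOPS subgroup, and the barriers of high priority are treated.
- Section 2.15 plans no analysis by subgroup.

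**The case against.** The strongest reply is that the ceiling of 100 comes from counting scales in an appendix that does not always reproduce its instruments in full. The Central Sensitisation Inventory is described in section 2.12 as a 25-point scale, yet nine items are printed, and the Örebro form itself announces more activities than it shows. This stands as a caveat on the zero figure. It does not rescue the rule, because Table 2 and section 2.12 both name a short form and nothing in the protocol shows extra items. If there are more items, the printed form needs correcting instead.

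A second reply is that Table 2 lists outcome measures and not classification tools, and that Appendix 2 names the Örebro without the short-form label, so the longer version may be meant. That is possible. But then a questionnaire that decides the treatment subgroup is neither scheduled, named by version nor printed. On either view the protocol needs a change.

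Two stronger readings go too far:

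- A reader might infer that section 2.10.1 contradicts Appendix 2 because it lists the subgroup with no Örebro condition. It does not. It gives names, sets out no criteria for any subgroup, and defers to Appendix 2. The most that can be said is that its stated basis, eligibility criteria and physical examination, leaves out a questionnaire score.
- A reader might infer that every patient without a class is forced into *Others*. The documents do not say so, since section 2.10.1 permits no label at all and *Others* is worded for a different pathoanatomical disorder.

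**Conclusion.** The criterion is wrong as written, and the severity is minor. On the form as printed, the required score is 6 points above the maximum and the subgroup is empty. This rests on two assumptions: that the printed ten-item form is the one used, and that its total is the plain sum of the items. The item codes and reverse-scoring marks point to a sum, but the protocol does not spell it out.

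The effect is confined to subgroup labels, fidelity checking and possibly subgroup-specific treatment in the STOPS arm. The number of patients concerned is unknown, because the protocol gives no expected subgroup sizes. It may be small: the discogenic classes need only 4 of 9 features, one of which is low back pain itself. A reader might infer that the trial's comparison is compromised. It is not: randomisation, outcomes and the between-group analysis do not use the label.

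**What to change.** Before the first patient is enrolled, do one of the following:

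- Replace the cut-off in Appendix 2 with one on the short form's own scale (ceiling 100), set by the STOPS developers. The documents give no short-form cut-off, and none can be derived from them. The cost is one line of text.
- Keep 105, administer at baseline the Örebro version to which it belongs, and name that version in Appendix 2, Table 2 and section 2.12. The cost is a small added burden for patients at baseline.

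In either case, check the printed form against the instrument in use, in particular the activities stem and the doubled wording of item 3. As a courtesy to the reader, add the questionnaire score to the basis for classification in section 2.10.1. Neither option affects the sample size or the analysis.
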